### Data collection

All patient data, including patient reported quality of life and clinical outcomes, will be entered into a paper-based case report form (CRF) and anonymised into Microsoft Excel for further analysis and monitored by the research and development department. Only the principal and co-investigators will have access to the full dataset.

### Study visits

Following screening and informed consent, a baseline visit will take place to record demographic data and medical history, prior to randomisation. Study visits will take place between post-op days 5 and 7, at post-op day 30 and at 6 months. Patients will be contacted both by post and telephone when arranging follow-up in order to maximise retention. At the study visits, information such as antibiotic use, length of hospital stay, visits to the general practitioner, dressing changes/number of dressings used and return to work or daily activities will be recorded by a non-blinded study nurse or doctor. Patients will be deemed to have returned to normal activities if they have returned to work (if they are of working age) or if they have returned to their pre-operative activity levels. In particular, patients will be asked if they have returned to driving, exercise or previous levels of social activity.

The same individual will remove the dressing in situ and dispose of it in an opaque bag. A second assessor, blinded to the dressing type, will be invited into the room in order to score the wound on the ASEPSIS scale. This will be recorded in the CRF. With the dressing removed, anonymous photographs will be taken of the wound, to be reviewed by an assessor not involved in trial recruitment or follow-up and used for the standardisation of ASEPSIS scores between participants. With the blinded assessor out of the room, the first study nurse or doctor will replace the dressing. Postal quality of life questionnaires will be sent to participants at 3 months and 6 months. Table 1 outlines the schedule of assessments.

**Table 1 Tab1:** Schedule of assessments (SPIRIT figure)

Visit	1	2	3	4	5	–	–
	Screening	Baseline assessment	Day 0- day of surgery	Day 5–7 post op	Day 30 post op ± 3 days	3 Months post-op ± 7 days	6 Months post-op ± 7 days
Screening questionnaire	X						
Patient information sheet	X						
Informed consent		X					
Baseline questionnaire		X					
SF-36		X		X	X	X	X
EQ-5D-3 L		X		X	X	X	X
GP letter		X					
RANDOMISATION FORM			X				
HPA surgical wound healing post discharge questionnaire					X		x
Clinical review of wound				X	X		X

*SF36* short form 36 utility, *EQ*-*5D* EuroQoL 5 domain utility index, *HPA* health protection agency

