**Methods:**

Patients undergoing clean or clean-contaminated vascular surgery will be randomised to have their surgical wounds dressed with a DACC-coated dressing or a non-coated occlusive absorbent post-operative dressing. All other aspects of their peri-operative care will be standardised or carried out in line with hospital policy. Wound assessments will be carried out between day 5–7, day 30 (± 3 days) and 6 months post-operatively (± 7 days) by a blinded assessor using the ASEPSIS scoring tool. Quality of life data using EQ-5D and SF-36, resource use and mortality data will also be collected. This feasibility trial will dictate the conduct of a full-scale trial through the collection of data on recruitment and retention rates, and fitness-for-purpose of the follow-up arrangements.

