## Introduction

The Centres for Disease Control and Prevention (CDC) defines a surgical site infection (SSI) as an infection within 30 days of an operation or up to 90 days if an implant is left in place and the infection is related to an operative procedure [1]. SSI’s occur in at least 5% [2] of patients and have a significant impact on patient morbidity, mortality and have subsequent time and cost implications [3].

Microorganisms causing SSI’s may be either endogenous (present on the patient) or exogenous (from the environment). The most common bacteria causing a superficial wound infection are those which are present on the skin of the patient. Deeper wound infections may be due to contamination of the wound by bacteria encountered during a procedure. Despite the reported incidence of SSI’s for clean surgery of 2.1% [4], the incidence in practice varies significantly. Open varicose vein surgery has an incidence of SSI’s reported in the literature which varies from 1.5 to 16% [5, 6] whilst figures from the surgical site infection surveillance demonstrated a high rate of SSI’s in patients undergoing lower limb amputation (13.1%) [7]. Conversely, SSI rates following carotid endarterectomy are reported as low as 0.2% [8, 9].

The Sorbact® range of dressings contains dialkylcarbamoylchloride (DACC), found in a spider’s web, which mediates the irreversible binding of bacteria that exhibit a high cell surface hydrophobicity (CSH). Large numbers of adherent or ‘trapped’ bacteria can then be removed from the wound at each dressing change. They are removed without disrupting the bacterial cell wall, thereby avoiding the resultant increase in inflammation observed with traditional antibiotics or antiseptics [10]. Numerous bacteria and fungi that exhibit CSH have been shown to attach to the DACC-coated material, including *Staphylococcus aureus*, *Pseudomonas aeruginosa*, *Enterococcus faecalis*, *Candida albicans* and the dermatophyte *Trichophyton rubrum* [11, 12].

DACC-coated dressings are available on the open market in both the UK via the National Health Service (NHS) supply chain, and the USA [13].

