#### Clinical outcomes—primary outcome

The primary outcome will be the incidence of SSI—measured by total ASEPSIS score ≥ 21 [19]—within 30 days of surgery, or as defined by the CDC definition of SSI [1, 20].

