### Blinding

Due to the nature of the treatment, a double-blind study is not possible (Leukomed® Sorbact® contains a coloured wound contact layer that is not present on standard dressings). To reduce the risk of bias, assessor reported outcomes, namely the ASEPSIS scoring of wounds, will be performed by a blinded assessor who will not have access to the patient notes. Anonymous photos of wounds will be rated by a third blinded assessor to reduce bias and ensure discrepancies in ASEPSIS scores are addressed. Bias in other outcomes will be limited by the use of predetermined objective measurements and bias in quality of life outcomes will be reduced by using patient-reported quality of life outcomes.

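### An infection that starts and settles between the day 5–7 and day 30 reviews can reach the primary outcome only through the CDC criterion, which the stated blinding does not cover

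*Protocol article*

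**What the plan says.** **Outcome.** In the section on the primary clinical outcome: "The primary outcome will be the incidence of SSI", "measured by total ASEPSIS score ≥ 21 [19]—within 30 days of surgery", "or as defined by the CDC definition of SSI". There are thus two ways to meet it. The Introduction says that the CDC "defines a surgical site infection (SSI) as an infection within 30 days of an operation", or up to 90 days where an implant is left in place. That is a definition over a period, not on a day.

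**Timing of the blinded score.** From the Abstract: "Wound assessments will be carried out between day 5–7, day 30 (± 3 days) and 6 months post-operatively". The Study visits section agrees: "Study visits will take place between post-op days 5 and 7, at post-op day 30 and at 6 months". Table 1 marks clinical wound review in the same three columns and none between them.

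**Blinding.** The dressings look different, so a double-blind design is ruled out. ASEPSIS scoring "will be performed by a blinded assessor who will not have access to the patient notes". A third blinded assessor rates anonymous photographs; the Study visits section places this person outside recruitment and follow-up. Blinded assessment is described for ASEPSIS scoring and for nothing else. For other outcomes the Blinding section relies on objective measures fixed in advance, which it does not name.

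**Data on the interval.** A non-blinded nurse or doctor records antibiotic use and GP visits at the study visits. Table 1 also schedules the "HPA surgical wound healing post discharge questionnaire" at day 30.

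**Use of the results.** The measured effect size is the first feasibility outcome, and the Sample size calculation section says that the pilot results will feed the final power calculation.

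**The concern.** The outcome is an incidence over 30 days, but the only blinded observations of the wound come near the start and near the end of that period. Take a patient whose wound is clean on day 6, is treated by the GP for infection on day 12, and has healed by day 30. The blinded scorer may see a sound wound both times and cannot consult the notes. The photographs do not help, because they are taken at the same visits.

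This infection can still count under the CDC criterion. The evidence for it would then come from the patient and from staff who know the dressing. In an open-label comparison, reporting a wound problem, seeking a GP's opinion and attributing an antibiotic course to the wound can all be influenced by knowing the arm.

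At stake is the credibility of the SSI difference that the pilot hands to the full trial. The protocol's own sample size section argues that infection is found more often when a blinded observer examines the wound. For most of the 30 days there is no such observer.

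**Working it through.** **1. The plan's own figure.** Inputs from the Sample size calculation and Statistical analysis sections: 19% v 10%, two-sided 5%, power 90%, 10% loss. Pooled-variance formula without continuity correction:

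n = [1.960·√(2·p̄·q̄) + 1.282·√(p₁q₁ + p₂q₂)]² / (p₁ − p₂)²

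With p̄ = 0.145: 2·0.145·0.855 = 0.24795 and p₁q₁ + p₂q₂ = 0.1539 + 0.0900 = 0.2439. The bracket is 0.976 + 0.633 = 1.609, so n = 2.588 / 0.0081 ≈ 319.6, that is 320. Then 640/0.90 = 711.1, or 712 in two equal groups. Both figures reproduce.

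**2. Days without a blinded score between the reviews.**
- Narrowest: scores on days 7 and 27 leave days 8–26, 19 days. In this case days 28–30 also fall after the second score.
- Widest: a score on day 5 and a second review on days 31–33 leave days 6–30, 25 days. Days 31–33 lie outside the 30-day window and are not counted.
- So 19/30 = 63% to 25/30 = 83% of the window.

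**3. Which route can count an interval infection?**

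| Route | Sees days 8–26? | Blinding stated? |
|---|---|---|
| ASEPSIS score at the visit | No | Yes |
| Photograph rating | No (taken at the visits) | Yes |
| CDC definition, from antibiotic and GP data | Yes, in retrospect | No; recorded by non-blinded staff |
| CDC definition, from the day-30 questionnaire | Yes, in retrospect | No; the patient can see the dressing |

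The two blinded routes do not cover the interval, and the two that cover it are not described as blinded.

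**4. Illustration of size.** Let f be the share of SSIs that start and settle between reviews. The documents do not give f; 10%, 20% and 40% are assumptions. The pilot has 144/2 = 72 per arm.

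*(a) None counted in either arm.* Rates become 0.19(1 − f) and 0.10(1 − f). Expected pilot events are 72·(p₁ + p₂). Power at 320 per group is Φ{[(p₁ − p₂)√320 − 1.960·√(2p̄q̄)] / √(p₁q₁ + p₂q₂)}.

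| f | Rates | Pilot events | Power at 320 per group |
|---|---|---|---|
| 0 | 19.0% v 10.0% | 20.9 | 90% |
| 10% | 17.1% v 9.0% | 18.8 | 86% |
| 20% | 15.2% v 8.0% | 16.7 | 81% |
| 40% | 11.4% v 6.0% | 12.5 | 68% |

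*(b) Counted in one arm only,* the extreme of differential detection.

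| f | Counted in control only | Counted in DACC only |
|---|---|---|
| 10% | 19.0 − 9.0 = 10.0 points | 17.1 − 10.0 = 7.1 points |
| 20% | 19.0 − 8.0 = 11.0 points | 15.2 − 10.0 = 5.2 points |
| 40% | 19.0 − 6.0 = 13.0 points | 11.4 − 10.0 = 1.4 points |

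The planned difference is 9 points. Table (b) gives outer bounds at each f, not an expectation.

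**The case against.** A reader might infer that interval infections are simply missed and scored as no SSI, so that the pilot's rates come out too low and the full trial loses power. The documents do not support that, for four reasons.

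- **The CDC criterion counts.** The day-12 patient is a candidate for it. Antibiotic use, GP visits and the day-30 questionnaire are collected. Readmission and re-intervention within 30 days are secondary outcomes, and adverse events are recorded throughout. An interval infection can be found in retrospect.
- **The figures in (a) need every interval case to be lost.** They also treat 19% and 10% as fully ascertained. Those rates come from an earlier study in the same centre whose review schedule is not given. If it used similar visits, discounting them again counts the loss twice.
- **The power calculation will be redone with pilot data.** If the full trial keeps the same endpoint, the observed rate is the right input, so a fall to 68% at a fixed 320 per group is not a consequence of this plan.
- **The article is condensed.** Who applies the CDC definition, and from which form, may be set out in a fuller document. That silence is not itself an error. Nor does the article list the components of ASEPSIS. If the score includes recent history, a scorer without the notes would still have to obtain it from the patient or from non-blinded staff.

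All four stand against the stronger reading. They do not remove the narrower point, which rests on what the article does state: the visit times, blinding described for ASEPSIS only, and interval data recorded by non-blinded staff. Listing the suitability of outcome measures as a feasibility outcome does not answer it either, because nothing stated would show how many SSIs the visit scores alone fail to find.

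**Conclusion.** The point holds in this form. Between the two reviews, 19 to 25 days of the 30-day window have no blinded wound score. An SSI confined to that gap is either uncounted or enters through the CDC criterion, on evidence outside the stated blinding. The main risk is detection bias in the pilot's SSI difference; under-counting is possible but not shown.

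The size cannot be fixed from the documents, because the share of SSIs that start and settle between visits is not given. The figures for events, power and bounds in the working are illustrations on assumed shares. The sample size of 320 per group and 712 in total is not in error. The conclusion assumes that ASEPSIS, as scored without the notes, reflects what is found at the review, and that no blinded assessment exists beyond what the Blinding section describes.

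**What to change.** Apply the CDC criterion through blinded classification, using people and data already in the trial.

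1. At day 30, prepare an extract for each patient with the arm and all dressing details removed, free text included: the post-discharge questionnaire, antibiotic courses with dates and reasons, GP visits for the wound, and any readmission or re-intervention.
2. Give it to the blinded photograph assessor, who is already outside recruitment and follow-up. This assessor decides whether there was a CDC-defined SSI and whether its onset was by day 30.
3. State in the primary outcome section that the outcome is met if ASEPSIS is 21 or more at either the day 5–7 or the day-30 review, or if there is a blinded-classified CDC SSI with onset by day 30. The second part specifies how the existing CDC criterion is applied; it is not a third criterion. The 90-day assessment for implant patients stays a secondary outcome.
4. Report by arm how many SSIs were found only by the second route. This gives the feasibility question on outcome measures a direct answer and replaces the assumed shares above with an observed figure.

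The cost is one extract form, a short addition to the outcome definition and some extra work for one assessor. No visit or procedure is added. Interval events would still rest partly on patient report, which redaction cannot make blind; what is removed is knowledge of the arm at the point of classification.

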### Trial exit

Patients will exit the trial after completing the 1-year follow-up visit, if they experience an adverse event or reaction deemed to require their withdrawal from the trial or if they choose to withdraw at any point during their inclusion in the trial.

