### Trial timescales

It is anticipated that the recruitment and treatment phase will be completed within 18 months. The primary endpoint is measured after 30 days, with all patients followed up for 6 months after entry into the trial.

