**Fig. 1 Fig1:**
[figure not shown]
Study flow chart. The target sample size for the pilot phase of this study is 144. Treatment and follow-up will run concurrently, giving a total time of 24 months from study start to completion

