### Statistical analysis

Data will be analysed on an intention to treat basis. The SPSS (IBM Corporation, Armonk, NY, USA) computer package will be used with a two-sided *p* value of < 0.05 taken as the level of significance. For feasibility outcomes, simple categorical data will be presented descriptively using mean (SD), median (IQR) for skewed data or *n* (%) for each group. Recruitment of a large trial within 18 months (based on rates observed in the pilot trial), and retention of 85% or better will be deemed acceptable.

Descriptive statistics (mean (sd) and *n* (%)) will be calculated for demographic and baseline characteristics of the patients. For the clinical outcome of SSI at 30 days, logistic regression analysis will be undertaken with SSI as the dependent variable and randomisation group as the independent variable. The model will be adjusted for confounding variables such as sex, age, BMI, smoking status, diabetes status and surgical site, as well as implant vs non-implant surgery. The regression model performance will be assessed by the Hosmer and Lemeshow test. Logistic regression will also be undertaken for satisfactory healing—total ASEPSIS score ≤ 10. For quality of life (EQ-5D-3 L and SF-36), an intragroup and intergroup analysis will be performed, using Friedman’s two-way analysis of variance (ANOVA) test to assess for intragroup differences, and Mann-Whitney *U* tests to assess for intergroup differences of the SF-36 responses. For the EQ-5D, responses will be dichotomised into ‘no problems’ and ‘problems’, and intragroup analysis conducted using related sample’s Cochrane’s Q test, with Pearson’s χ^2^ tests for intergroup analysis. For time to event data (time to return to work and mortality), Kaplan-Meier and long rank tests will be used to calculate and compare event rates between groups, followed by a cox regression to adjust for confounding variables.

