The AE reporting period for this trial begins as soon as patients have consented to the trial and ends at the point of discharge from the trial, following a final study visit or telephone consultation at 1 year following surgery. The health status of subjects will be checked at each study visit. The investigator will record all directly observed AEs and all AEs spontaneously reported by the trial subject. A pre-existing condition (i.e. a disorder present at the baseline study visit and noted on the baseline medical history/physical examination form/medical notes) is not to be reported as an AE unless the condition worsens or episodes increase in frequency during the AE-reporting period. All adverse events (serious and non-serious) will be recorded by the investigator in patient’s data collection forms (CRFs) using R&D’s adverse event report form. All adverse events will be recorded by the investigator in patients’ medical records/notes. All AEs will be followed-up by investigators until the event has resolved or a decision has been taken for no further follow-up.

If a clinically significant abnormal laboratory value occurs, this abnormality will be recorded as an adverse event/reaction.

The investigator will report fatal or life-threatening SAEs or serious adverse reactions (SARs) to the research ethics committee (REC) within 7 days and follow-up information within a further 8 days by following the request on the serious event initial and follow-up report forms. The investigator will send all other SAE or SAR reports to the REC within a maximum of 15 days.

Patients have access to information on the complaints procedure for obtaining compensation following harm through non-negligence or negligence as a result of participating in the trial.

Study completion refers to the date of final data collection from the last patient. Paper records from the trial will be stored for 5 years from trial end.

An end of study declaration form will be submitted to the REC and Trust R&D within 90 days from completion of the trial and within 15 days if the trial is discontinued prematurely. A summary of the trial report/publication will be submitted to the REC and Trust R&D within 1 year of the end of trial.

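### Follow-up and adverse-event reporting end at 1 year in two sections but at 6 months everywhere else, and the exit rule can also cost 30-day outcome data

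*Protocol article*

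**What the plan says.** Two places in the protocol article put the end of participation at 1 year:

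- *Trial exit* gives this rule: "Patients will exit the trial after completing the 1-year follow-up visit, if they experience an adverse event or reaction deemed to require their withdrawal".
- *Monitoring, safety and quality control*: the AE reporting period closes on discharge from the trial, "following a final study visit or telephone consultation at 1 year following surgery".

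The places that set the schedule stop at 6 months:

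- *Trial timescales*: the primary endpoint is at 30 days, "with all patients followed up for 6 months after entry into the trial". The same section expects that the "recruitment and treatment phase will be completed within 18 months".
- *Study visits* and Table 1: post-operative visits at days 5–7, day 30 and 6 months, with postal questionnaires at 3 and 6 months. The last column of Table 1 is 6 months.
- Fig. 1 legend: treatment and follow-up overlap, "giving a total time of 24 months from study start to completion".

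*Trial exit* lists two other routes out. One is the patient's own choice. The other applies "if they experience an adverse event or reaction deemed to require their withdrawal from the trial". Under *Statistical analysis*, "Data will be analysed on an intention to treat basis", and retention of at least 85% is the threshold for acceptability.

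**The concern.** The end of follow-up fixes three things: when a patient has completed the trial, how long adverse events must be collected and reported, and when retention is counted. With two end points, each of these has two answers. A serious event at month 9 is inside the reporting period on one reading and outside it on the other. A patient seen at 6 months and not afterwards is retained on one reading and lost on the other. In a feasibility trial, retention is one of the results that decides whether a full trial is judged workable.

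The second matter is what leaving the trial means. The exit sentence does not separate stopping the dressing from leaving follow-up, and it lists adverse-event exit apart from the patient's own withdrawal. Follow-up could therefore end for someone who is still willing to be assessed. The AE definition in the safety section is broad enough to include a wound infection, so the reason for exit may be related to the primary outcome.

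**Working it through.** **Step 1. Reproduce the stated total.** The inputs are 18 months for recruitment and treatment (*Trial timescales*) and 6 months of follow-up (same section). Assume that the last patient enters at the end of the 18 months.

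- Total = recruitment phase + follow-up of the last patient = 18 + 6 = 24 months. This matches the Fig. 1 legend.
- With exit at 1 year: 18 + 12 = 30 months, which is 6 months more than stated.

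The stated total therefore fits only the 6-month end point.

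**Step 2. AE window.** Reporting closes at 12 months after surgery and the last scheduled visit is at 6 months: 12 − 6 = 6 months. The safety section has health status checked at each study visit and otherwise relies on observed or spontaneously reported events. Between months 6 and 12, collection would rest on spontaneous reports and on a 1-year contact that neither the visit list nor Table 1 contains.

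**Step 3. Retention.** The pilot target is 144 patients and the criterion is 85%: 0.85 × 144 = 122.4, so at least 123 must be retained. The denominator is the same on either reading. What changes is the time at which the numerator is counted, and losses after 6 months count only on the 1-year reading.

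**Step 4. Does any outcome need 1-year data?** The primary outcome is at 30 days. The listed secondary outcomes name 30 days, 90 days, 3 months or 6 months where they give a time point; time to return to activity or work gives none. No outcome names 1 year.

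**Step 5. Exit for an adverse event.** Set the sections side by side:

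- *Trial exit* ends participation, not only the dressing, when an event is judged to make withdrawal necessary.
- Surgical site infection is counted to 30 days, and to 90 days for implant patients.
- *Statistical analysis* specifies intention to treat, which is only as good as the outcome data on those randomised.

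An exit of this kind before day 30 (or day 90) can leave the infection outcome unassessed. No expected number of such exits is given, so no effect can be calculated.

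**The case against.** **On the end point.** A journal article condenses the full protocol, and the safety section does name a visit or call at 1 year, so it would be wrong to say that no such contact is mentioned anywhere. Both points are fair. But this is not a detail left out: the article states two incompatible end points, and the 1-year one appears twice. The consequences are also limited, since the primary endpoint and the sample size do not depend on the choice.

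**On adverse-event exit.** A reader might infer that the rule removes patients with adverse events, contradicts intention to treat and biases the comparison towards no difference. The documents do not support this.

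- Exit is confined to events judged to require withdrawal. No section says that infection is such an event.
- Nothing says that data are deleted. Withdrawal produces missing data; it does not by itself contradict analysis in the randomised arm. Withdrawal and missing-data rates are themselves listed feasibility outcomes.
- An infection recorded as an adverse event goes into the case report form and is followed until it resolves or a decision is taken to stop.
- The direction of bias is not fixed. Suppose a fraction *f* of infected patients left unscored; any value of *f* is an assumption without a source in the documents. Observed risk is p(1 − f)/(1 − pf), so observed odds are p(1 − f)/(1 − p). With the planning rates of 19% and 10% and equal *f* in both arms, (1 − f) cancels and the unadjusted odds ratio stays at (0.19/0.81)/(0.10/0.90) = 2.11. The risk difference does shrink, from 9 points to 7.3 at f = 0.25 (15.0% v 7.7%) and 5.2 at f = 0.5 (10.5% v 5.3%). The planned model, however, is logistic regression. If *f* were 0.25 in one arm only, the odds ratio would be 2.11 × 0.75 = 1.58 (control) or 2.11/0.75 = 2.81 (DACC), so the bias can go either way.

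What remains is narrower. Following an adverse event to resolution is not the same as continuing blinded ASEPSIS assessment, and the text does not say that the latter goes on.

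**Conclusion.** The first point holds on the text alone. Two sections end the trial at 1 year, while the follow-up statement, the visit list, Table 1 and the 24-month total end at 6 months. The gap is 6 months per patient and 6 months of trial duration (30 against 24). It leaves the safety window, the exit point and the retention time point undefined, so it should be corrected, although it touches neither the primary endpoint nor the sample size. The only assumption is that total duration means recruitment plus follow-up of the last patient, which reproduces the stated figure.

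The second point holds in a limited form. Adverse-event exit without withdrawal of consent can lose infection outcomes that the intention-to-treat analysis needs, possibly for reasons linked to the outcome. This weakens that analysis without contradicting it. How often it would happen, and which way it would push the estimate, cannot be determined from the documents.

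**What to change.** **End of follow-up.** Use one end of follow-up and AE reporting in *Trial timescales*, the Fig. 1 legend, *Study visits* with Table 1, *Trial exit* and *Monitoring, safety and quality control*. There are two consistent ways to do this:

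- Change the 1-year references in *Trial exit* and the safety section to the 6-month visit. This loses no listed outcome and keeps the 24 months.
- Keep 1 year, add that contact to the visit list and Table 1, amend *Trial timescales*, and restate the total as 30 months.

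In either case, name the time point at which the 85% retention criterion is counted.

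**Exit after an adverse event.** Reconcile *Trial exit* with *Statistical analysis* by stating that, for any patient who stops the allocated dressing, outcome assessment continues and the patient is analysed in the randomised arm, unless the patient withdraws consent to follow-up. This concerns data collection only; no rule on when a dressing should be stopped is proposed.

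**Cost.** The 6-month option is a text amendment only; the 1-year option adds a contact and 6 months. The exit wording means continued follow-up of a few patients no longer using the trial dressing.
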